### Data Collection and Management

All study participants will be assigned a study identification number. CRFs will be completed on paper forms. Data will then be entered and stored in a password-protected electronic database. The original paper copies of CRFs and all study data will be stored in a locker within the study site, accessible to the involved researchers only.

### Statistical Analysis

All analysis will be conducted on an intention-to-treat basis, including all patients in the groups to which they are randomized for whom outcomes are available (including drop-outs and withdrawals). Descriptive statistics will be used to summarize baseline characteristics. The Student *t* test will be used to compare mean values of continuous variables for approximating a normal distribution. For nonnormally distributed variables, the Mann-Whitney U test will be used. The chi-square or Fisher exact test will be used, when appropriate, to compare percentages. For continuous outcomes, differences in means or differences in medians (depending on the distribution of the data), and for dichotomous outcomes, the RR and number needed to treat, all with a 95% CI, will be calculated. The difference between study groups will be considered significant when the *P* value is <.05, when the 95% CI for RR does not include 1.0, or when the 95% CI for MD does not include 0. All statistical tests will be 2-tailed and performed at the 5% level of significance. Two independent reports (rotavirus-vaccinated and nonvaccinated children) are planned.

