### Power Calculation

The primary outcome of the study is the duration of diarrhea. Based on available data in the literature, the average duration of gastroenteritis in children is 5 to 7 days [3]. We assume that a clinically significant difference in the effectiveness of *L reuteri* DSM 17938 versus placebo will shorten the duration of symptoms by 24 hours (±24 hours). To detect such a difference in the duration of diarrhea between the study groups with a power of 90% and alpha of 0.01, a sample of 60 children is needed. Assuming approximately 20% loss to follow-up, we aim to recruit a total of 72 children for this study. A similar sample size for rotavirus vaccinated and nonvaccinated children is planned. Sample size calculations were performed with StatsDirect version 2.3.8 (StatsDirect Ltd).

At the Department of Paediatrics of St Hedwig of Silesia Hospital, there are 300 admissions of children with diarrhea per year and the same number of such patients who present to the emergency room. Assuming that 20% of these children will be eligible for the study, we will achieve adequate participant enrollment to reach the target sample size during 1 year of recruiting for rotavirus nonvaccinated children. Recruitment of rotavirus-vaccinated children may be slower (up to 2 years). In Poland, rotavirus vaccination has been recommended since 2006; however, vaccine reimbursement is not available. Hence, currently, the rotavirus vaccination coverage rate is low (12.7% [23] to 30% [24]), likely due to the high vaccine cost.

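### Skewed durations get a Mann-Whitney P value but an interval for the difference in medians, a different and less precise quantity (minor)

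*Protocol article*

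**What the plan says.** All of this stands in the Statistical Analysis section of the protocol article.

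- **Test:** "For nonnormally distributed variables, the Mann-Whitney U test will be used".
- **Effect measure:** "differences in means or differences in medians (depending on the distribution of the data". The same sentence attaches an interval to every measure: "the RR and number needed to treat, all with a 95% CI, will be calculated".
- **Significance rule:** P<.05, or a relative risk interval that excludes 1, "or when the 95% CI for MD does not include 0". The Introduction and the Abbreviations both define MD as mean difference.
- **Level:** "All statistical tests will be 2-tailed and performed at the 5% level of significance".

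The section names no method for the median-difference interval and no location-shift estimate. It does not say what to conclude if the test and the interval point in different directions.

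**The concern.** The Mann-Whitney test compares whole distributions by ranks. If the arms differ by a shift, the estimate that belongs to it is the Hodges-Lehmann shift, which is the median of all between-arm pairwise differences. The difference between the two sample medians is another statistic. With right-skewed data and about 30 children per arm, it is noisier.

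This branch could well carry the primary result. Duration of diarrhea is a positive time. The 2012 placebo-controlled trial summarised in the Introduction reports 3.3 (SD 2.1) versus 2.1 (SD 1.7) days. SDs that large relative to the means make right skew likely.

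At stake is a report whose P value says there is an effect while the adjacent interval includes no effect, and an effect size stated less precisely than the data allow.

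**Working it through.** **Inputs.** The Power Calculation section gives the planned effect, "will shorten the duration of symptoms by 24 hours (±24 hours", read here as a difference of 24 h with SD 24 h. It also gives "with a power of 90% and alpha of 0.01, a sample of 60 children is needed" and "Assuming approximately 20% loss to follow-up, we aim to recruit a total of 72 children for this study". Allocation is 1:1 (Study Design).

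**The plan's own figure.** n per arm = 2(z₀.₉₉₅ + z₀.₉₀)²(SD/difference)² = 2(2.576 + 1.282)²(24/24)² = 29.8, so 30 per arm and 60 in all. The plan's figure is reproduced. 60 × 1.2 = 72, or 36 per arm before losses. Both 30 and 36 per arm are used below.

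**Width, in closed form.** For a shift between arms with density f, the large-sample ratio of the median-difference interval's width to the Hodges-Lehmann interval's width is √[3(∫f²)²/f(median)²]. For a log-normal with log-scale SD s this becomes √(1.5·exp(s²/2)):

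- s = 0.38 (mean 60 h, SD 24 h): 1.27
- s = 0.7: 1.38

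**Simulation.** Times are continuous log-normal hours (an assumption), with 1,500 or more trials per scenario. Each trial compares three things:

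1. Mann-Whitney P<.05.
2. Whether a 95% percentile-bootstrap interval for the median difference excludes 0.
3. Whether the Hodges-Lehmann interval excludes 0. This interval runs from the k-th smallest to the k-th largest of the mn pairwise differences, with k = ⌊mn/2 − 1.96√(mn(m+n+1)/12)⌋. For m = n = 30, k = ⌊450 − 132.6⌋ = 317.

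| Scenario | P value vs bootstrap median CI disagree | P value vs Hodges-Lehmann CI disagree |
|---|---|---|
| 72 vs 54 h, CV 0.5 | 17-19% | under 1% |
| Shift 16 h, SD 24 h, 30 per arm | about 19% | under 1% |
| Means and SDs of the 2012 trial | about 13-16% | under 1% |
| Planned: 24 h, SD 24 h, 30 per arm | about 5-8% | under 1% |
| Planned: 24 h, SD 24 h, 36 per arm | about 2-5% | under 1% |

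Nearly all conflicts are P<.05 with a median interval that includes 0. In the first scenario at 36 per arm, Mann-Whitney was significant in 69% of trials and the bootstrap median interval excluded 0 in 52%. Mean widths were 31.9 h and 25.1 h. The ratio is 31.9/25.1 = 1.27, so the Hodges-Lehmann interval is 1 − 25.1/31.9 = 21% narrower.

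**Sensitivity.**

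- *Interval method.* With an analytic standard error (Price-Bonett) in place of the bootstrap, disagreement at 30 per arm is 22.3% + 1.5% = 23.8% for the 16 h shift and 7.4% + 0.1% = 7.5% for the 24 h shift.
- *Shape.* The extra width is 46-50% for exponential times but only 5% for a symmetric heavy-tailed (Laplace) shape.
- *Ties.* With durations rounded to whole days, Hodges-Lehmann also disagrees with the test, in about 40% of trials in one scenario and over 50% in another run.

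**The case against.** **Error rate.** A reader might infer that the plan accepts either the P value or the median interval as proof, which would lift false positives above 5%. Such a rule would give roughly 5-8% under no effect, depending on the interval method. The document does not state that rule. Its interval criterion for continuous outcomes names only MD, which is the mean difference. For a skewed outcome the only stated criterion is therefore P<.05 at the 5% level. For normal outcomes, the t test and the usual t interval agree by construction. No inflation follows from the text.

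**Unstated construction.** The interval method could sit in a fuller document. If the authors meant the Hodges-Lehmann shift, only the label is wrong. This is fair, and it is one reason the point is minor. The words as printed still name a difference in medians, and a reader cannot infer the other meaning.

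**Design point.** At the planned effect most trials agree. With durations of 5 to 7 days and SD 24 h, a Shapiro test flagged at least one arm in only about a third of simulated trials, so the t-test branch would often apply. This also stands. The mismatch matters mainly at smaller effects or larger SDs.

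**Other outcomes.** A reader might extend the point to watery stools per day and duration of intravenous rehydration. That fails. At 36 per arm, under assumed shapes, Hodges-Lehmann disagreed with the test in 47% of trials for Poisson counts of 3 versus 2, and in 56% for zero-inflated durations. The median interval disagreed in 53% of trials in both cases, so there is no real gain.

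**Estimand.** A difference in medians is legitimate and easy for clinicians to read. Without a pure shift, the two measures also target slightly different values: 16.1 h and 15.3 h in the 72 versus 54 h scenario. Part of the choice is therefore preference. The mismatch with the chosen test is not.

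**Conclusion.** The point holds in limited form and is minor. For nonnormal continuous outcomes, the plan pairs a rank test with an interval for a quantity that the test does not address. For right-skewed durations in hours, this gives contradictory results in about 13-19% of trials at moderate effects or larger SDs, and in about 2-8% at the planned effect. The interval is about 20-30% wider than the matching one.

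These sizes rest on log-normal shapes, untied times, a bootstrap interval, and reading ±24 h as an SD. None of these is fixed by the document except that the diary records stool times, which makes an hour scale feasible. The stated 5% error rate is not affected.

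**What to change.** In the Statistical Analysis section, state the following:

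- Duration of diarrhea is computed in hours from the stool times in the diary.
- Where Mann-Whitney is used on it, the effect is the Hodges-Lehmann shift, with the 95% CI obtained by inverting that test, in place of the difference in medians.
- Medians per arm are tabulated as description.
- The P value of the named test decides significance, and the interval describes the effect.

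The cost is one or two sentences and standard software output, with no added patients, visits or data. There are two small downsides. The Hodges-Lehmann shift is less familiar to clinicians, which the tabulated medians offset. Its agreement with the test is lost under heavy ties, so the change should not be presented as a remedy for counts, day-rounded times or mostly-zero outcomes. The wording should be settled before unblinding.

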### Monitoring

The study will be carried out in accordance with the approved protocol. *L reuteri* DSM 17938 is being safely used worldwide for a number of indications, and the US Food and Drug Administration applied to it the Generally Recognized as Safe status [25]. Still, an independent Data and Safety Monitoring Board (DSMB) will be set up prior to the start of the study. The DSMB will review data after recruitment of 25%, 50%, and 75% of subjects to review the study progress and all adverse events.

### Harms

Although the occurrence of adverse events as a result of participation in the current trial is not expected, data on adverse events will be collected. All serious adverse events will be immediately reported to the study coordinators who will be responsible for notifying the Ethics Committee, all participating investigators, and the manufacturer of the study products.

## Results

The recruitment started in January 2017 and is planned to be finalized in June 2018 for rotavirus nonvaccinated children. The recruitment of rotavirus-vaccinated children may be slower due to a relatively low coverage rate in Poland. Data analysis and submission to a peer-reviewed journal is expected within 3 months after completion of the study.

## Discussion

### Summary

This study will add to the current knowledge on the efficacy of *L reuteri* DSM 17938 for the management of AGE. Children vaccinated and not vaccinated against rotavirus will be evaluated separately.

### Strengths and Limitations of This Study

A strength of the study is its study design (randomized controlled trial), which is the most robust methodology to assess the effectiveness of therapeutic interventions. The findings of this randomized controlled trial, whether positive or negative, will contribute to the formulation of further recommendations on the use of *L reuteri* DSM 17938 for the treatment of AGE in children. A limitation is that stool volume, one of the objective ways of assessing the efficacy of antidiarrheal drugs, will not be assessed. In addition, the recruitment of rotavirus-vaccinated children may be slow due to a relatively low coverage rate in Poland, likely due to the high vaccine cost.

## Appendix

Multimedia Appendix 1 CONSORT-EHEALTH checklist (v1.6.1).

## Abbreviations

AGE: acute gastroenteritis
ASF: Amsterdam Stool Form
BSF: Bristol Stool Form
CFU: colony forming units
CRF: case report form
DSMB: Data Safety and Monitoring Board
ESPHGAN: European Society of Pediatric Gastroenterology, Hepatology, and Nutrition
MD: mean difference
RR: relative risk
